### Data analysis

Quantitative data analysis would be conducted using SPSS v26. The socio-demographic characteristics of participants would be summarized in frequencies and percentages. Continuous data gathered would be scrutinized for normality and necessary transformation would be applied if needed. Continuous variables would be summarized using means and SD. Mann-Whitney test or its parametric equivalent (if possible) would be employed to analyses the difference stroke self-efficacy levels in both groups at same points of follow-up evaluation. A Friedman test or its parametric equivalent (if possible) would be employed to ascertain changes in stroke self-efficacy level over the time. Results would be classified as significant if p <0.05 (two-tailed). All qualitative transcripts exported to NVivo version 10 would be analyzed by reading that data line by line and making noting down insights as meaning units while the reading is ongoing. The meaning units would be labeled with a code, this would be done repeatedly to capture all aspects of the content (data). The codes would then be categorized into sub-categories and broader categories for identification of themes [44]. Both quantitative and qualitative data would be compared to identify similarities and differences for the purpose of convergence.

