### Randomization, allocation and blinding

After eligible participants have provided informed consent and undergone baseline screening, they would be randomly assigned to the intervention group (Nurse-led rehabilitation support + Treatment as usual) and control group (only treatment as usual).

Randomization would be conducted by an independent researcher who is not involved in the study. She will use a combination of block and stratified randomization to assign 40 participants to either the intervention group or the control group. Prior to the assignment, participants would be stratified based on the type of stroke (hemorrhagic vs ischemic). Within each stratum, participants will be assigned using block randomization with block size of four. Additionally, the independent researcher would generate random sequence for the block order with an online random sequence generator (sealedenvelope.com). The sequence numbers would be written and placed in opaque envelopes by the independent researcher. Immediately a participant signs the consent form, the principal investigator ([name]) would inform to sequentially open the envelope in the corresponding block and assign participant to the group indicated in the envelope.

Participants will not be blinded to the assigned group. Also, It will not be possible to blind the interventionists (stroke nurses and other health professionals) providing the intervention in this study. Essentially both parties (participants and interventionists would be unmasked. However, the assessors of study outcomes would be blinded to the allocation of participants. Also, assessors gathering baseline data on self-efficacy and any other data after group allocation would be blinded to the allocation status of participants.

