### Data collection, entry and management

Data would be gathered from participants before the intervention but after recruitment and after the intervention. Baseline data would be gathered on two occasions prior to the intervention. Before randomization, data on participant demographic characteristics, patient history, functional status, psychological functioning and cognitive capacity would be gathered. Baseline data on patient’s self-efficacy would be collected before the first session of the intervention via phone survey. The second phase of data collection would take place immediately after the end intervention capturing quantitative date on user satisfaction, qualitative data on experiences throughout the intervention only for participants in the intervention group and stroke-self efficacy levels for participants in both group. The third and final phase of data collection would be executed 4 weeks and 12 weeks after the intervention respectively capturing stroke efficacy levels in both groups. The data collection process would be undertaken by an independent assessor who are unaware of participant allocation. After completing each phase of data collection, the quantitative data would be entered into a spreadsheet using Microsoft Excel. The data would be processed for outliers and missing inputs. Qualitative interviews would be audiotaped, audios would be saved in a PC folder and later transcribed for analysis. The entered information and saved audios would be protected by a password only accessible by the research team.

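### The SSEQ arm comparison ignores baseline score and stroke type and so loses precision, and the time-only Friedman test cannot show an intervention effect; adjustment is clean only if baseline SSEQ is taken before randomisation

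*Protocol article*

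**What the plan says.** The protocol article (Data analysis) fixes the SSEQ analysis by name.

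- **Between arms:** a Mann-Whitney test or its parametric equivalent "would be employed to analyses the difference stroke self-efficacy levels in both groups at same points of follow-up evaluation". Data collection, entry and management gives three such points: end of intervention, then 4 and 12 weeks later.
- **Over time:** "A Friedman test or its parametric equivalent (if possible) would be employed to ascertain changes in stroke self-efficacy level over the time". The section does not say whether this is run in each arm or on both arms together.
- **Threshold:** two-sided p<0.05. No covariate, stratum term, change score or arm-by-time term is named.

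Two relevant variables are nevertheless available. Randomisation is stratified by stroke type (Randomization, allocation and blinding). A baseline SSEQ is also taken: "self-efficacy would be collected before the first session of the intervention via phone survey". Data collection lists this separately from the data gathered before randomisation. The randomisation section speaks of self-efficacy baseline data gathered after group allocation by blinded assessors, and says that participants know their group.

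The secondary objective (Conceptual framework) is to measure whether the intervention would improve self-efficacy.

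**The concern.** The natural parametric equivalents of the two named tests are a two-sample t-test and a one-way repeated-measures ANOVA. Falling back on them therefore adds neither baseline nor stratum, and no comparison of the arms over time.

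Two things are at stake. First, a trial of 40 people gives up precision on its only clinical outcome, when the abstract says the findings are meant to inform a larger study. Second, the Friedman test answers a question other than the objective. Participants enter from 1 week after stroke (Eligibility criteria), the intervention lasts 6 months, and both arms receive physiotherapy (Intervention). Scores may well rise in both arms whatever the intervention does, and a significant time effect would not separate that from benefit.

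**Working it through.** **Inputs from the article.** 20 per group and 20% attrition per group (Proposed sample size); 1:1 allocation; one baseline and three follow-up SSEQ measurements. Completers per arm: 20 × (1 − 0.20) = 16. The article gives no SD, effect size, power or precision for SSEQ, so it has no figure of its own to reproduce here.

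**Assumptions.** The correlation r between baseline and follow-up SSEQ is not given; 0.3, 0.5 and 0.7 are shown. Results are in SD units. The stroke-type stratum is credited with no gain, because its link to SSEQ is unknown.

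**1. Precision of the arm difference at one visit.** Half-width = t(0.975, 30) × √[(2/16) × (1 − r²)], with t = 2.042 and √(2/16) = 0.3536. The sample-size equivalent is 1/(1 − r²). Power is a normal approximation for an assumed true effect of 0.8 SD.

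| Analysis | 1 − r² | Half-width (SD) | Sample-size equivalent | Power at 0.8 SD |
|---|---|---|---|---|
| Unadjusted | 1 | 2.042 × 0.3536 = 0.72 | 1.00 | 62% |
| Adjusted, r = 0.3 | 0.91 | 0.69 | 1.10 | 66% |
| Adjusted, r = 0.5 | 0.75 | 0.63 | 1.33 | 74% |
| Adjusted, r = 0.7 | 0.51 | 0.52 | 1.96 | 89% |

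The unadjusted row is for the t-test. A Mann-Whitney test on normal data has about 60% power in the same case. The one or two degrees of freedom spent on covariates change the half-widths by about 0.002 SD.

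**2. Validity of the planned arm comparison.** Randomisation makes the arms equal at baseline in expectation, so the expected arm difference at follow-up equals the expected arm difference in change. In simulated trials with no effect (16 per arm, 2,000 runs per setting), each single Mann-Whitney test rejected in 4% to 5%.

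**3. Friedman test with no intervention effect.** Simulation with 16 per arm, four visits, equal correlation between visits, and the same recovery in both arms. The test is run in the intervention arm alone unless stated.

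| Assumed common recovery | Correlation | Significant |
|---|---|---|
| 0.5 SD, all by first follow-up | 0.5 / 0.7 | 37% / 57% |
| 0.5 SD, spread linearly over visits | 0.5 / 0.7 | 29% / 44% |
| 0.5 SD, either shape | 0.3 | 20% to 27% |
| 0.2 to 0.3 SD | 0.3 to 0.7 | 7% to 23% |
| 0.8 SD, all by first follow-up | 0.5 / 0.7 | 77% / 94% |
| 0.5 SD, all by first follow-up, both arms pooled | 0.5 / 0.7 | 71% / 91% |

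The rate runs from near nominal to near certain, depending on inputs the article does not supply. In no row does it carry information about the intervention.

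**4. Timing of the baseline.** The two passages on baseline SSEQ, read together, place the phone survey after allocation, with participants who know their arm reporting their own confidence. If that knowledge shifts the answers, the baseline score is partly a result of allocation, and conditioning on it can bias the arm effect. A follow-up-only comparison does not condition on that score.

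**The case against.** The best defence is that the planned arm comparison is sound. Each Mann-Whitney test addresses the secondary objective and holds its level, and that level already allows for chance baseline imbalance. This stands. A reader might infer that the plan never tests the intervention, or that its comparison is biased; the documents support neither, since the comparison is randomised and unadjusted.

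A reader might also infer that the Friedman test will often yield a false claim of benefit. The article states its purpose only as "would be employed to ascertain changes in stroke self-efficacy level over the time". It does not say the result will be read as an intervention effect, and the frequency depends on an assumed size and shape of recovery. What stands is that the test cannot supply evidence about the intervention.

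Three further points have weight. The gain is slight if r is near 0.3, which is possible across a 6-month intervention starting soon after stroke. Adjusting for the baseline as now timed could do harm. And multiplicity over three visits and the handling of missed visits are commonly left to a statistical analysis plan, so they are not counted against the article here.

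That this is a feasibility trial with an admitted small size (Limitations) lowers the weight of the point but does not answer it: a small sample is a reason to recover precision where it costs no recruitment.

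**Conclusion.** The point holds as one of efficiency and interpretation. The article commits to an arm comparison that leaves out baseline SSEQ and the stratification factor, and to a time test with no arm term. Adjustment would narrow the interval by about 5%, 13% or 29% (1 − √(1 − r²)) at r = 0.3, 0.5 or 0.7. These figures assume 16 completers per arm and a linear relation between baseline and follow-up; any contribution from stroke type is unknown. The precision gain can be taken cleanly only if baseline SSEQ precedes allocation. The importance is moderate: SSEQ is secondary, and no conclusion on retention, adverse events, resources or satisfaction depends on it.

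**What to change.** 1. Move the baseline SSEQ survey to before randomisation, alongside the demographic, functional, psychological and cognitive data already gathered then.
2. Analyse SSEQ at the three follow-ups with one linear mixed model containing arm, visit, arm-by-visit, baseline SSEQ and stroke type. Include every participant with at least one follow-up, in the arm assigned.
3. Report the adjusted arm difference with its 95% confidence interval at each visit, with end of intervention as the main time point.
4. Keep the unadjusted Mann-Whitney test as a sensitivity analysis.
5. Present change over time within arms as description only.

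**Cost.** No extra participants or visits, and SPSS v26, already named, fits the model. The phone survey has to happen earlier, which is a change of procedure and not only of analysis wording. The model assumes roughly normal residuals, which the sensitivity analysis helps to check. If the baseline correlation proves low, little precision is gained.

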## Methods and analysis

### Study design

The trial is a parallel-group (intervention and control groups) randomized controlled study with 1:1 allocation to assess feasibility of a nurse-led telerehabilitation intervention administered remotely at the homes of Ghanaian stroke survivors. Post intervention process evaluation will employ a mixed method approach to exploring feasibility elements of the intervention.

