### Proposed sample size

We aim at recruiting 20 participants per group (total = 40 participants). The size however is guided by Julious’ rule of thumb for 12 participants per group in pilot trial [42]. The potential attrition rate estimated is 20% per group. During the follow-up phase, qualitative data on participant experiences through one-on-one interviews would be captured from 15 conveniently sampled participants from the intervention group. According to Hennick and Kaisser [43] a 15 sample is appropriate for reaching data saturation. An interview guide designed for purpose who be used to gather needed data.

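### The over-time test of self-efficacy uses only participants with all four scores, so at the protocol's own 20% attrition about 16 of 20 per arm are analysed and the others' observed scores are discarded

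*Protocol article*

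**What the plan says.** Four self-efficacy assessments are scheduled in the protocol article, under Data collection, entry and management:

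- Baseline: "Baseline data on patient’s self-efficacy would be collected before the first session of the intervention via phone survey".
- Immediately after the intervention: "stroke-self efficacy levels for participants in both group".
- Two later follow-ups: "The third and final phase of data collection would be executed 4 weeks and 12 weeks after the intervention respectively capturing stroke efficacy levels", again in both groups.

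Under Proposed sample size, the target is 20 per group (40 in total), and "The potential attrition rate estimated is 20% per group".

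Under Data analysis, two kinds of test are named for this outcome. Mann-Whitney tests, or a parametric equivalent, compare the arms at each follow-up. For the time course: "A Friedman test or its parametric equivalent (if possible) would be employed to ascertain changes in stroke self-efficacy level over the time". The software is SPSS v26. The only statement on missing values is in the data-management section: after spreadsheet entry, the data will be processed for outliers and missing entries. No imputation method is named.

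**The concern.** The Friedman test ranks each participant's scores against one another across the visits, so it needs a complete row. Repeated-measures ANOVA, the usual parametric counterpart, needs the same. One missed assessment therefore removes the participant from the analysis, along with every score already collected.

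The protocol itself expects one in five to be lost, over 6 months of intervention and a further 12 weeks of follow-up. Two things follow:

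- Data that participants gave are not used, in a trial with only 20 per arm.
- The over-time result describes completers, while the Mann-Whitney result at each visit describes whoever attended it. The two self-efficacy analyses then refer to different people. If leaving is related to earlier self-efficacy, the completers' curve is not the curve of the randomised participants.

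**Working it through.** **Inputs from the protocol.** 20 per arm, 1:1 allocation; 20% attrition per group; four assessments; Friedman test or parametric equivalent.

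**The protocol's own size.** The rule of thumb it cites is 12 per group. Inflated for 20% loss, this gives 12 / (1 − 0.20) = 15, not 20. The protocol says only that 20 is guided by the rule and gives no formula, so this is not an arithmetic error. Nothing below depends on it.

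**Participants analysed.** 20 × (1 − 0.20) = 16 per arm; 2 × 16 = 32 of 40. Four per arm are dropped.

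**Check of the deletion.** In a 20 × 4 data set with 4 last-visit values missing, Friedman with the incomplete rows omitted gave a statistic of 2.025 (p = 0.567), identical to the test on the 16 complete rows. A standard repeated-measures ANOVA routine refused the unbalanced data. This was run in general statistical software, not SPSS.

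**Scores discarded per arm**, if all 4 drop-outs leave at the same point. The 16 completers supply 16 × 4 = 64 scores.

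| Leave before | Scores held per drop-out | Discarded per arm | Collected per arm |
|---|---|---|---|
| End of intervention | 1 | 4 | 68 |
| 4 weeks | 2 | 8 | 72 |
| 12 weeks | 3 | 12 | 76 |

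In the middle row, for example, the Mann-Whitney test at the end of intervention would use 20 per arm and the later ones 16, while the Friedman test would use 16 throughout.

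**Missed single visits (assumed rates).** If 5% or 10% of the 16 also miss each of two other follow-ups, 16 × 0.95² = 14.4 or 16 × 0.90² = 13.0 per arm remain.

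**Bias (assumptions: SD 1, equal correlation ρ between visits, no true change, 20% leave).** If the lowest-scoring 20% at one visit leave, the mean of those remaining shifts at that visit by φ(0.842) / 0.80 = 0.280 / 0.80 = 0.35 SD. At every other visit it shifts by 0.35ρ. The spurious change is therefore:

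- Leaving depends on the end-of-intervention score: baseline to end, +0.35(1 − ρ), or +0.21, +0.14 and +0.07 SD at ρ = 0.4, 0.6 and 0.8. Baseline to either later visit, 0.35ρ − 0.35ρ = 0.
- Leaving depends on the baseline score: baseline to any later visit, −0.35(1 − ρ), or −0.21, −0.14 and −0.07 SD.

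With weaker dependence (logistic drop-out, slopes 0.7 to 1.5 per SD, 400,000 simulated subjects, ρ from 0.4 to 0.8), the change is 0.03 to 0.14 SD, with the same signs.

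**Effect on the test.** Simulating arms of 20 with ρ = 0.6, where the 4 lowest at end of intervention then leave, gave a spurious rise of 0.13 SD. Friedman rejection at 0.05 went from 4.8% to 7.1%.

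**Scale.** The standard error of a mean change with 16 participants is √(2(1 − ρ)/16): 0.27, 0.22 and 0.16 SD at ρ = 0.4, 0.6 and 0.8. Even the extreme bias (0.21, 0.14, 0.07) stays below one standard error.

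**The case against.** **Missing-data handling belongs in the analysis plan, which is not shown.** True, and its absence here is not the point. The point concerns a test that the protocol names. The data-management sentence on missing entries could mean imputation, which would keep every row, so deletion is not certain. But it names no method, follows spreadsheet entry and reads as data cleaning.

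**The parametric equivalent could be a mixed model.** This is possible but not the usual meaning, and the Friedman test would remain in the plan beside it. If a mixed model is intended, saying so settles the matter for that branch.

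**The stakes are low.** This stands. Self-efficacy is the secondary outcome of a feasibility trial, the Limitations section already says the sample may be too small to detect differences, and retention is itself a primary outcome, so the loss will be measured. The Mann-Whitney comparisons lose no observed follow-up score to this deletion.

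**The remedy swaps a rank test for a normal-theory model.** This stands in part. An unstructured covariance over four visits has 10 parameters, which is demanding with 20 per arm. If drop-outs leave before the second assessment, the model recovers only one baseline score each.

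**Stronger readings that do not hold.** A reader might infer that the completers' curve must exaggerate improvement. It need not: the sign reverses if leaving follows a low baseline score, and the documents do not say which mechanism applies. A reader might also infer that the analysis falls below 12 per group. On the protocol's own figure 16 remain. Getting to 16 × 0.90³ = 11.7 takes three further assumed 10% losses that no document supports, and the 12 is a rule of thumb for pilot size, not a requirement of this test.

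**Conclusion.** The point holds as a modest flaw in a named secondary analysis. At the stated 20% attrition, and unless missing scores are imputed, the over-time test rests on about 16 of 20 per arm. It discards 4 to 12 observed scores per arm, depending on when the four leave. These counts follow from the protocol's own figures and the complete-row requirement.

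The bias is conditional. It arises only if leaving depends on earlier self-efficacy, its sign depends on which score drives it, and its size of roughly 0.03 to 0.2 SD rests on assumed correlations and drop-out models. The recruitment, retention and satisfaction results are not affected. The change is worth making because it is cheap, not because the trial's main conclusions are at risk.

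**What to change.** In Data analysis, make the over-time analysis a likelihood-based repeated-measures model (SPSS MIXED) with visit as a factor, by randomised arm, fitted to all observed self-efficacy scores of all randomised participants. Specify a parsimonious covariance such as compound symmetry if an unstructured one does not fit. Report the number contributing at each visit. Keep the Friedman test as a completers-only sensitivity analysis, with its n shown.

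The cost is a few words in the protocol and slightly more analysis in software already named; no new data are needed. The downside is reliance on missing at random and approximately normal residuals in a small sample. The gain is small if most drop-outs leave before the end-of-intervention visit.

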### Possible risks and mitigation

There are minimal perceived risks to study participants involved in the intervention. However, all participants would undergo periodic risk assessments to unearth potential risks of adverse outcomes. The assessment would be carried out in their homes by the research investigators. Additionally, participants and their caregivers would be provided emergency dial lines and the contacts of the researchers in case of an adversity. In case of an adverse event such as falls or emotional collapse, the researcher (and stroke nurse/ other rehabilitation health worker) working with the patient at moment would immediately assess the situation, notify emergency support if participant is in immediate danger (e.g. ambulance service, national suicide hotlines and participant’s emergency contact) for immediate assistance and continue to engage with the participant and/or their caregivers until help arrives. If the participant is not in immediate danger, they would be referred to the University of Ghana Hospital for further assistance. All adverse events related to the intervention would be well-documented, reported to clinicians in charge and reviewed. Additionally, the research team has liaised with community health nurses to provide assessment and further recommendation for patients in their homes.

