**Aim:**

The primary objective of the study is to test the feasibility of a nurse-led telerehabilitation intervention in improving self-efficacy among stroke survivors. The findings of the trial are intended for use in a future larger study.

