### Intervention

Eligible participants would randomly be assigned to either the treatment or control group. Participants in control group would receive treatment as usual (TAU) which comprise of two weekly in-person physiotherapy sessions and two sessions with a medical doctor at the University of Ghana Hospital Participants in the control group would receive upper and lower limb physical rehabilitation and undergo medical review (medication review and symptom management) with medical doctors.

Participants in the intervention group would receive comprehensive nursing neurorehabilitation support in addition to existing service at the hospital (treatment as usual). The components of the intervention are guided by relevant literature, established guidelines [29–31] and have been reviewed by a panel of experts including two neuroscience nurses, two community health nurses, three neurologists, one stroke specialist, one physiotherapist and a stroke survivor. Patients would undergo assessment and receive various therapies in appropriate domains for 6months. A follow-up evaluation would be performed at the end, 30- and 90-days after the intervention (S2 Fig). The intervention would involve the following components;

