### Outcomes and outcome measures

#### Primary outcomes

Based on the CONSORT checklist [37] the pilot study is primarily aimed at assessing the preliminary feasibility and acceptability of the intervention in the Ghanaian context.

*Feasibility*. Feasibility would be measured by retention rate, rate of adverse events and recording the details of resources used in implementing the intervention. Additionally, duration of sessions and cost of internet for the research team and study participants would be captured.

*Participant satisfaction*. This will include the use of a 12-item Patient Satisfaction with Telehealth questionnaire to assess the level of satisfaction of participants on delivery of the intervention, time spent, quality of audio-visual channels involved and overall perceived benefits [38].

Factors influencing user satisfaction: Qualitative data of participant experiences and in-depth factors that influence their rate level of satisfaction would be captured in order to provide in-depth explanation of satisfaction levels. This would be guided by an interview probe designed for purpose.

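### The sentence that commits to documenting adverse events covers only intervention-related ones, which is narrower than the unrestricted adverse event rate listed as a primary feasibility measure

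*Protocol article*

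**What the plan says.** Under Primary outcomes, the protocol article states: "Feasibility would be measured by retention rate, rate of adverse events and recording the details of resources used in implementing the intervention". The adverse event rate there carries no limit to related events and none to one arm.

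Under Possible risks and mitigation, the commitment to document events reads: "All adverse events related to the intervention would be well-documented, reported to clinicians in charge and reviewed". No other sentence in the article says that adverse events will be documented.

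The same section also says that "all participants would undergo periodic risk assessments to unearth potential risks of adverse outcomes", and adds: "The assessment would be carried out in their homes by the research investigators". Participants and caregivers receive emergency numbers and the researchers' contacts. The examples given of an adverse event are falls and emotional collapse.

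Under Intervention, controls receive usual care only: "two weekly in-person physiotherapy sessions and two sessions with a medical doctor". Under Data collection, entry and management, the last two follow-ups are "executed 4 weeks and 12 weeks after the intervention respectively capturing stroke efficacy levels in both groups", and adverse events are not named at any phase. Under Data analysis, the planned between-group test "would be employed to analyses the difference stroke self-efficacy levels in both groups at same points of follow-up evaluation"; no between-arm analysis of adverse events is described. The abstract's Aim states: "The findings of the trial are intended for use in a future larger study".

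**The concern.** Two statements about the same quantity differ in scope. The outcome is a rate of adverse events. The documentation commitment is a rule about related events.

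The restriction acts in two ways. A control who falls at home has not been exposed to the intervention, so that fall cannot meet the condition. In the intervention arm, a fall meets it only after someone has judged it to be related. Applied literally, the rule would give a count filtered by relatedness and drawn from one arm, in a trial where participants and interventionists know the allocation.

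Falls and distress also occur after stroke without this intervention, so relatedness is hard to judge case by case without a usual-care rate for reference. The randomised control group can supply that rate, and the planned larger study would want it. The scope has to be settled at collection: an event that was never recorded may not be recoverable later, and a related-only count cannot be converted to an all-event rate when the share judged related is unknown.

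**Working it through.** The article states no adverse event rate, threshold or safety sample size, so there is no figure to reproduce. The check is a comparison of scope, followed by an illustration.

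**Scope, side by side**

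| Group of events | Primary outcomes (adverse event rate) | Possible risks and mitigation (documentation sentence) |
|---|---|---|
| Intervention arm, judged related | included | covered |
| Intervention arm, judged unrelated | included | not covered |
| Control arm, any cause | included | not covered, because controls do not receive the intervention |

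One of three groups is covered. The risk assessments of all participants are directed at potential risks, and the text does not say that they record events. Data collection, entry and management adds no adverse event item.

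**Illustration of size**

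Input from the article: 20 participants per arm (Proposed sample size). Assumptions: 10% to 40% of participants have at least one event, and a share s of affected intervention-arm participants have an event judged related. Neither figure is in the article.

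1. Controls with an event outside the sentence = 20 × p_control. At 10%: 20 × 0.10 = 2. At 40%: 20 × 0.40 = 8.

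2. Share of all affected participants whom the sentence covers = s × p_int / (p_int + p_control). The most favourable case is s = 1:
   - equal risks: 1/2 (2 of 4 at 10%; 8 of 16 at 40%)
   - intervention risk half the control risk: 0.5 / 1.5 = 1/3
   - intervention risk double the control risk: 2 / 3

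3. A related-only count does not identify the all-event risk. Documented count = 20 × p_int × s:
   - p_int = 10%, s = 100%: 20 × 0.10 × 1.00 = 2
   - p_int = 40%, s = 25%: 20 × 0.40 × 0.25 = 2

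   The same 2 of 20 fits a true risk of 10% or of 40%.

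**Precision if everything is recorded**

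Wilson 95% intervals for one arm: 2/20 gives 2.8% to 30.1%; 8/20 gives 21.9% to 61.3%. For 4/20 against 4/20, the Newcombe 95% interval for the difference is about −25 to +25 percentage points. The rates could be estimated by arm, but only roughly.

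**The case against.** The strongest reply is that the sentence describes how events are handled and is not the data-collection rule. It sits among the emergency steps, and it concerns reporting to clinicians and review. The commitment to measure is the one under Primary outcomes, which is unrestricted, and a narrow escalation rule can stand beside a broader count. There are also detection routes that are not limited by arm: the home risk assessments, the contact numbers, and the controls' own physiotherapy and doctor visits. An article also condenses a full protocol, which may hold the event form and name who judges relatedness.

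Much of this stands. A reader might infer that control events will not be recorded, that there is no basis for recording them, or that the larger study will have no background rate. The documents do not support those readings. A promise to document related events does not say that others are discarded, and the primary measure is itself a reason to collect them. The unnamed judge of relatedness and the missing form are details that an article may leave out, so they are not part of this point. Nor is there a planned between-arm test that would be biased.

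One can also argue that the rate is meant to describe the intervention alone, since resources and session length are listed alongside it. That is plausible, but the text does not say so. Even on that reading, events judged unrelated in the intervention arm remain outside the documentation sentence.

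What the reply does not remove is that the restriction is stated in the text, and that it is narrower than the article's own primary measure.

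**Conclusion.** The point holds as a mismatch of scope. The documentation sentence, followed as worded, covers neither control events nor intervention-arm events judged unrelated, while the primary adverse event rate is unrestricted. It does not show that those events will be lost.

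The size cannot be established from the article. Under the assumed risk of 10% to 40% in each arm, 2 to 8 of 20 controls would have an event outside the sentence, and at most half of all affected participants would be covered. That bound becomes one third or two thirds if the intervention-arm risk is half or double the control risk. These figures show what literal application would do; they do not predict what staff will do. One of several primary feasibility measures is affected, and no sample size, significance level, retention, satisfaction or self-efficacy result changes. The change is a cheap improvement, best made before events start to accrue.

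**What to change.** Reword the sentence under Possible risks and mitigation so that all adverse events in both groups, whatever their cause, are documented, reported to the responsible clinicians and reviewed. Record relatedness as a separate field, so that it describes an event and does not decide whether the event is counted.

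Ask about events in the same words and at the same times in both arms, using contacts already planned: the periodic risk assessments, and the follow-up assessments at the end of the intervention and 4 and 12 weeks later. At the follow-up assessments, ask only after the self-efficacy questionnaire is complete, so that an answer cannot reveal the allocation to the blinded assessor before scoring. An answer at one visit could still reveal it before the next, so having another team member ask is safer where staffing allows.

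Report the rate by arm, descriptively, as all events with related events as a subset. Mark events noticed only during intervention sessions, because those sessions give the intervention arm more chances of detection.

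The cost is one changed sentence, one added question and a short form for 40 people. There will be more events to record and review, many of them probably unrelated, and some recall error between contacts. With 20 per arm the by-arm rates stay imprecise and should not be tested.
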